### Data confidentiality

Data entered in REDCap will not capture any personal identification and will be known by a unique identifier. Only the recruiting healthcare provider and the research coordinator employed for the trial will have contact details of the trial participant and the immediate family member to facilitate their follow-up. The name of the trial participant and phone number will be visible in the app that will be accessible only to healthcare providers. However, when the data are extracted from the app for fidelity analysis, the identifiers will not be extractable by the trial manager. The data contained in the app will be stored in a high security server accessible only to designated technical team leaders of the sponsors via a dedicated wide area network service. The server undergoes daily back-ups, with daily snapshot recovery points and 30 days’ retention. Anonymous participant data will be stored in REDCap and archived as per institutional archival policy. Qualitative data will be stored securely with restricted access on the sponsor server. The data in the app platform will be destroyed 5 years after completion of the trial.

### Patient and public involvement

During the development of the TReAT intervention, patients who had undergone knee arthroplasty and their family members were involved in pilot testing the different components of the TReAT app—the education material, exercise videos and diary questions. Patients were not involved in deciding on the choice of outcome, trial follow-up or any aspects of conduct of the study. However, during the conduct of this trial, bimonthly newsletters will be shared with all trial participants to provide an update on trial progress. Stakeholder consultations will be held to share findings and gain end user feedback on the usability and implementation of the TReAT app. A lay summary using infographics will be shared with trial participants via a newsletter at the end of the study.

### Statistical methods

#### Statistical methods for primary and secondary outcomes

Effectiveness outcomes: Baseline characteristics including mean, SD, number and percentage will be described. Mean group differences and 95% CI of KOOS-ADL score at 3 and 6 months adjusted for baseline score will be calculated using mixed effect linear regression. A p value of 0.025 will be considered as statistically significant for each of the time points. The analytical approach will be modified intention-to-treat, which includes all those who were randomised irrespective of their adherence to trial protocol if they had at least one follow-up visit after enrolment. This approach will exclude those who were lost to follow-up after enrolment.

All secondary continuous outcomes that include KOOS-Pain, ROM and performance-based measures will be compared at 3 and 6 months using linear mixed effect method adjusted for baseline KOOS-ADL, as performance-based measures will not be collected at baseline. A statistical analysis plan will be developed before the end of trial recruitment and made publicly available before final analysis. No interim analysis will be performed. The preplanned subgroups are gender and laterality of index surgery (bilateral/unilateral). Effect modification will be claimed based on interaction p<0.05. We will not perform a per-protocol analysis. Multiple imputation of missing primary outcome will be done only if more than 5% of enrolled are lost to follow-up. All analyses will be done in Stata (StataCorp) and R version 4.4.1 or higher (Postit Team, 2025).

Process evaluation: App usage (usage of diary, type of exercise prescribed and number of times therapy was modified) will be presented graphically along with suitable summary measures. The written research coordinators’ notes will be quantified using a fidelity checklist. Transcripts of qualitative interviews will be coded independently in NVivo software (Lumivero (2023) NVivo (V.14)), using an inductive-deductive approach followed by thematic analysis. The qualitative findings from the interviews, fidelity checklist, rehabilitation adherence and knowledge score, and functional outcomes will be triangulated to understand the mechanistic pathway to change, whether intervention use/non-use led to different outcomes. Further, contextual factors affecting the implementation and usage of the intervention will be summarised.

Cost analysis: Costing components will be considered from the patients’ perspective in both groups. We will assume equivalent costs for surgery, surgery-related in-hospital stays and medication in both groups and hence, costs for these components will not be collected. However, costs associated with any re-hospitalisation following discharge, either related to index surgery or other medical reasons, will be included in the analysis. Only patients who undergo unilateral or bilateral knee arthroplasty will be included in the cost analysis, and patients who will undergo knee arthroplasty of the other knee during the trial period will be excluded.

Responses to EQ-5D-5L will be converted to a single-index utility score using the Indian value set and converted into QALYs.^23^ QALY is based on the single utility score which defines the valuation of health-related quality of life from a patient’s perspective on a scale indicating 0 as ‘dead’ and 1 as ‘perfect health’. Assuming a linear trend in a patient’s utility scores from the baseline to each follow-up time point, the area under the resulting curves indicates the QALYs experienced by that patient at 6 months.^24 25^

The average of resource use, costs and EQ-5D-5L utility scores for both trial groups will be reported along with suitable method of dispersion. Comparison of cost and utility scores between two groups will be reported as mean difference and 95% CI. Bootstrapping methods will be used to address the expected skewed nature of these variables. We will report the incremental cost-effectiveness ratio representing the difference in cost for an additional QALY gained and cost per 5° knee flexion gained in the intervention group compared with usual care. Time-saving potential of the app-supported intervention as compared with the usual care will also be compared.

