### Outcomes

Primary outcome: Early recovery of knee function is one of the desired outcomes by patients undergoing knee arthroplasty.^14^ The primary outcome knee function will be assessed using the ADL subdomain of Knee Injury and Osteoarthritis Outcome Score (KOOS). It is a validated tool to evaluate post knee rehabilitation interventions^15^ and will be completed by the trial participants at baseline (before surgery status), 3 and 6 months after surgery in both groups. The total score ranges between 0 and 100 and the minimum clinically important group difference for this domain ranges from −1.5 to 15.5 units.^16^ The KOOS-ADL questionnaire will be self-administered in paper during the follow-up visit by the patient. If the patient is not able to complete it by self, then the family member will assist in eliciting the responses from the patient. In the absence of a family member, an independent assessor, not involved in the intervention implementation and rehabilitation, will administer the questionnaire. The primary comparisons would be to compare the end value of KOOS-ADL score at 3 and 6 months independently between the two groups adjusted for baseline score.

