### Sample size

The primary endpoints are group differences in self-reported knee function measured using the KOOS-ADL at 3 and 6 months using mixed-effect linear regression. The KOOS-ADL score ranges from 0 to 100 with higher scores indicating better function. We aim to detect a difference of at least 7 points,^16^ and a common SD of 15 points was assumed. The sample size was estimated assuming two-sided, two-sample equal-variance t-test, with an overall type I error rate (α) of 0.05. The effect size is defined as d=(μ1−μ2)/σ, where σ is the common SD for both groups. To detect a population effect size of 0.40 with 85% marginal power, the number of needed participants will be around 150 in each group after adjusting for 10% loss to follow-up and multiplicity due to two primary time points using Bonferroni’s correction. The sample size was computed using PASS 2023, V.23.0.2. We expect to reach the target sample size in 18 months.

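### The two primary comparisons are tested at 0.025 each but reported with 95% confidence intervals, so for p between 0.025 and 0.05 the interval and the decision disagree

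*Protocol article*

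**What the plan says.** The Outcomes section makes the two primary comparisons separate: the plan is to "compare the end value of KOOS-ADL score at 3 and 6 months independently between the two groups", adjusted for baseline. The Sample size section assumes a "two-sided, two-sample equal-variance t-test, with an overall type I error rate (α) of 0.05", and the number of participants allows for "multiplicity due to two primary time points using Bonferroni’s correction". The Statistical methods section carries this through to the analysis: "A p value of 0.025 will be considered as statistically significant for each of the time points".

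The sentence just before that one fixes what is reported for the same two comparisons: "Mean group differences and 95% CI of KOOS-ADL score at 3 and 6 months adjusted for baseline score", from a mixed-effects linear regression. The article mentions no 97.5% or multiplicity-adjusted interval, and it does not say that the 95% intervals are unadjusted or descriptive.

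**The concern.** A two-sided 95% interval excludes zero exactly when p is below 0.05, and a 97.5% interval does so exactly when p is below 0.025. The plan uses the first for reporting and the second for deciding. A primary result with p between 0.025 and 0.05 would then carry two opposite messages: an interval that suggests a difference and a formal statement that none was shown. Readers and later reviewers often judge by the interval. If they do so here, they apply 0.05 at each time point and lose the multiplicity control for which the trial enlarged its sample.

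Both numbers are stated in the article, so this is not a detail left to the statistical analysis plan.

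**Working it through.** **Inputs.** From the Sample size section: SD 15, design effect 0.40, 85% marginal power, overall two-sided alpha 0.05 split over two time points, 10% loss, about 150 per group. The same section gives a target of 7 points, and 7/15 = 0.467, so both effect sizes are carried below. The correlation between the 3- and 6-month test statistics is not given; 0.5 to 0.7 is assumed for the familywise figures.

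**1. Reproduce the plan's sample size.** n per group = 2 × ((z for 0.0125 upper tail + z for 85% power)/d)² = 2 × (3.278/0.40)² = 134.3, so 135. Dividing by 0.9 gives 150. At alpha 0.05 the same steps give 113, or 126 after loss. The stated 150 therefore rests on 0.025 per time point, and that threshold is deliberate.

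**2. Interval half-widths.** With 150 × 0.9 = 135 analysed per arm, SE = 15 × √(2/135) = 1.826 points. With 268 degrees of freedom:

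| Interval | t quantile | Half-width (points) |
|---|---|---|
| 95% | 1.969 | 3.59 |
| 97.5% | 2.254 | 4.12 |

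The ratio is 4.12/3.59, about 1.14 to 1.15 (2.241/1.960 = 1.144 with normal quantiles). An observed difference between about 3.6 and 4.1 points gives a 95% interval that excludes zero beside a non-significant result. These figures are unadjusted. The planned analysis adjusts for baseline, and any reduction in SE would move this window towards zero and narrow it.

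**3. How often the two disagree.** The probability is P(|Z| > 1.960) − P(|Z| > 2.241), where Z is normal with mean d × √(135/2) and SD 1.

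| True effect d | Mean of Z | P(p < 0.05) | P(p < 0.025) | Clash per time point |
|---|---|---|---|---|
| 0 | 0 | 5.0% | 2.5% | 2.5% |
| 0.40 | 3.286 | 90.8% | 85.2% | 5.6% |
| 7/15 | 3.834 | 97.0% | 94.4% | 2.5% |

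For a clash at one or both time points, simulation with the same effect at both and correlation from 0 to 0.9 gives 9.8 to 10.8% at d = 0.40 and 4.5 to 5.0% at 7/15.

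**4. Familywise error under the global null.** The stated rule (p below 0.025 at each time point) gives at most 4.9% if the tests are independent (1 − 0.975² = 0.0494), and 4.6 to 4.3% at correlation 0.5 to 0.7. Judging by whether either 95% interval excludes zero gives 9.1% at correlation 0.5 and 8.3% at 0.7.

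**5. Holm, as an option.** Holm tests the smaller p at 0.025 and, if that is significant, the other at 0.05. By simulation with 135 per arm and correlation 0.5 to 0.7, Holm raises power per time point from about 85% to 89% at d = 0.40, and from about 94% to 96% at 7/15. Power to win at least one time point is the same under both methods (94.4% at correlation 0.5 and 92.3% at 0.7, for d = 0.40).

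**The case against.** The best defence is that the decision rule is explicit and tied to the p value. It matches the Sample size section and controls the familywise error. On this view the 95% intervals are only conventional display, and the statistical analysis plan, promised in public before the final analysis, can say so. Most of this stands, and it limits the point to reporting and interpretation. It does not remove the mismatch, because the article itself sets the 95% level for the primary comparisons and says nothing about how to read it.

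Two stronger readings are tempting, and the document supports neither.

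- A reader might infer that the trial's type I error is inflated to 8 or 9%. It is not: that figure applies only to someone who sets aside the stated rule and judges by the intervals, and it depends on correlations that are assumed.
- A reader might infer that Bonferroni is itself a mistake, because Holm would recover power at no cost, above all the power to show benefit at both time points. Bonferroni is valid, prespecified, consistent between the two sections and already paid for in the sample size. No section makes success at both time points the objective. The primary objective is to compare the groups at 3 and 6 months, the comparisons are made independently, and the sample size aims "To detect a population effect size of 0.40 with 85% marginal power". An alpha split implies that either time point can succeed. Holm also has a cost: it has no simple matching confidence intervals, and an interval level that depends on the step reached would give up the simultaneous coverage that 97.5% intervals provide.

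**Conclusion.** The mismatch is real, and it is small. The plan pairs tests at 0.025 with intervals at 95%, so for p between 0.025 and 0.05 the reported interval contradicts the declared result. Before adjustment this concerns observed differences of about 3.6 to 4.1 points, with a probability per time point of about 5.6% if the true effect is 0.40 and about 2.5% if it is 7/15 or zero. These figures assume SD 15, 135 analysed per arm and no gain from baseline adjustment. The formal error control of the trial is intact. The case for acting is that the remedy is nearly free and can be in place before any result is seen. The choice of Bonferroni over Holm is not an error in the plan.

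**What to change.** State in the statistical analysis plan that the 3- and 6-month KOOS-ADL differences will be reported with 97.5% confidence intervals, matching the 0.025 threshold. If 95% intervals are also shown, label them as unadjusted for the two time points and not used for the decision. The cost is one or two sentences and primary intervals about 14% wider; the sample size, the tests and the data collection do not change.

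Optionally, the team may replace single-step Bonferroni with Holm at overall alpha 0.05. It keeps the familywise error at 5% and brings the gains per time point shown in the working, but nothing for winning at least one time point. If Holm is adopted, keep the 97.5% intervals as the simultaneous intervals, and say that a second time point declared significant at 0.05 may have a 97.5% interval that includes zero.

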#### Inclusion criteria

Adults (aged ≥18 years) scheduled for primary, partial or total (unilateral or bilateral) knee arthroplasty indicated for knee osteoarthritis.Individuals with access to a smartphone and internet connection.Individuals, or any of the family members living in the same household, who can navigate a smartphone and use common features such as video calling, messaging and camera.Individuals able to speak and read English or Hindi language.

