### Assignment of interventions

Permuted varying block randomisation with 1:1 allocation ratio stratified by trial site was generated using Stata V.18 (StataCorp. 2023. Stata Statistical Software: Release 18., StataCorp) by an independent statistician, not involved in the recruitment process. Varying block size was used to minimise predictability due to the open-label nature of the trial. The randomisation scheme will be implemented using the interactive web randomisation feature of REDCap managed centrally at the sponsor institute. Following informed consent and baseline data collection, the research coordinator will log into REDCap using site specific user credentials to randomise the participant. The group allocation will be made available on confirmation of eligibility and informed consent. Automatic real-time system-generated notification of the group assignment will be sent to the trial investigators and research coordinator. All participants will be in the trial for 6 months after enrolment. They will be followed up at 3 and 6 months after randomisation.

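### The stated mixed models name neither site nor laterality as covariates, so a small and nearly free gain in precision is left unclaimed

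*Protocol article*

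**What the plan says.** The Outcomes section sets the primary comparison: "compare the end value of KOOS-ADL score at 3 and 6 months independently between the two groups adjusted for baseline score". The statistical methods section repeats it for the mixed-effect linear regression: "Mean group differences and 95% CI of KOOS-ADL score at 3 and 6 months adjusted for baseline score". For the secondary continuous outcomes the same section again names one covariate, baseline KOOS-ADL, because the performance tests are not done at baseline.

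Randomisation is described under Assignment of interventions as "Permuted varying block randomisation with 1:1 allocation ratio stratified by trial site". No other stratification factor is given.

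The inclusion criteria admit patients "scheduled for primary, partial or total (unilateral or bilateral) knee arthroplasty indicated for knee osteoarthritis", so the trial mixes one-knee and two-knee operations. In the analysis of clinical outcomes, laterality appears only beside gender as a subgroup factor, with the rule "Effect modification will be claimed based on interaction p<0.05".

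The article also says: "A statistical analysis plan will be developed before the end of trial recruitment and made publicly available before final analysis". That plan is not at hand.

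**The concern.** The article does not leave the adjustment set open. It names a covariate for the primary models in two places and for the secondary models in one, and each time it is baseline KOOS-ADL alone. A statistical analysis plan that simply followed this text would leave out two factors known at randomisation.

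**Site.** Blocks within site keep the arms close to balanced across the two hospitals, one publicly and one privately funded. If outcome differs by site and the model omits site, that difference stays in the residual variance although the design has largely removed it from the group comparison. The reported interval is then too wide. The regression is called mixed-effect, so site might be meant as a random effect, but the text does not say so.

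**Laterality.** Baseline KOOS-ADL describes the patient before surgery. If recovery differs between one and two operated knees, that difference arises later, and the baseline score need not absorb it. The stair, walk, timed-up-and-go, chair-rise and single-leg tests have no baseline value of their own, so more unexplained variance may remain there.

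What is at stake is the width of the confidence interval, not the validity of the comparison.

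**Working it through.** **1. The plan's own figure.** Inputs from the Sample size section: effect size 0.40, SD 15, power 85%, overall two-sided α 0.05 halved to 0.025 per time point, 10% loss.

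n per arm = 2(z₀.₉₈₇₅ + z₀.₈₅)²/d² = 2(2.241 + 1.036)²/0.40² ≈ 134.3, rounded up to 135. Then 135/0.90 = 150, as stated. (The exact t-test version gives 136, or 152 after loss.) No variance reduction from any covariate enters this figure.

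An effect size of 0.40 at SD 15 is 6 points, so the power figures below refer to 6 points. The same section also names 7 points, and 7/15 is 0.467. That is a separate matter and does not affect this one.

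**2. Precision without further covariates.** SE = 15√(2/135) = 1.83 points. Power for 6 points at α 0.025 is 85.2%.

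**3. Effect of adding laterality.** The documents give neither the bilateral share p nor the KOOS-ADL gap L between bilateral and unilateral patients. Both are assumptions here: p from 0.1 to 0.5 and L from 2 to 10 points.

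- Share of variance explained: R² = p(1−p)L²/15²
- Residual SD = 15√(1−R²)
- SE = residual SD × √(2/135)

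| p | L | R² | SE | Power | N per group after loss |
|---|---|---|---|---|---|
| any | 0 | 0 | 1.83 | 85.2% | 150 |
| 0.1 | 2 | 0.2% | 1.82 | 85.3% | 150 |
| 0.2 | 5 | 1.8% | 1.81 | 85.9% | 147 |
| 0.3 | 5 | 2.3% | 1.80 | 86.1% | 147 |
| 0.3 | 10 | 9.3% | 1.74 | 88.7% | 136 |
| 0.5 | 10 | 11.1% | 1.72 | 89.3% | 134 |

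Worked mid-range row: 0.3 × 0.7 × 25/225 = 0.0233; 15√0.9767 = 14.82; 14.82 × √(2/135) = 1.80.

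The 95% half-width is 1.96 × 1.826 = 3.58 points unadjusted. It becomes 1.96 × 1.804 = 3.54 mid-range and 1.96 × 1.721 = 3.37 at the top of the range.

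**4. Chance imbalance.** Under simple randomisation, the between-arm difference in bilateral share has SD √(2p(1−p)/135). Multiplied by L, this shifts the unadjusted difference with SD 0.07 to 0.61 points, or 0.28 mid-range. The 95% ranges are ±0.14 to ±1.19, and ±0.55 mid-range. This is part of the SE of 1.83 in step 2 and must not be added to it.

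**5. Site.** The same R² formula applies, with p the share recruited at one site and L the gap between sites. The documents give neither. With equal recruitment, which is an assumption, gaps of 2, 5 and 10 points give R² of 0.4%, 2.8% and 11.1%.

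**6. Limit of the calculation.** It uses the total SD of 15 and takes no account of the baseline score already in the model. Any part of the laterality or site effect already present in baseline KOOS-ADL would reduce the gain. Where those effects are unrelated to baseline, they would explain a larger share of the smaller residual variance.

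**The case against.** The strongest reply is that a full covariate list belongs in the statistical analysis plan, which is promised, and that nothing in the article excludes further terms. That stands in part: the plan may already contain both factors, and then the point is closed. But the article fixes a model rather than staying silent, so the unseen plan would have to depart from the stated text.

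A second reply is that every input to the size of the gain is assumed and that the gain is mostly small. That stands. It also applies to gender, the other subgroup factor, for which no gap is given either. Laterality is proposed because it is a feature of the operation itself, whose effect on recovery the pre-surgery score need not carry.

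A third reply is that a standard interaction model already contains the laterality main effect. That is so, but the subgroup model does not supply the primary estimate.

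A reader might infer more than the documents support:

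- **That laterality is a declared prognostic factor.** It is listed as one of two subgroups. A subgroup asks about effect modification; it does not state that the factor predicts outcome.
- **That randomisation should have been stratified by laterality.** Naming a subgroup creates no such duty, and recruitment began in June 2024.
- **That chance imbalance in bilateral cases biases the result.** It does not. Randomisation keeps the comparison valid, and the SE already includes this variation.
- **That the trial is underpowered without the adjustment.** The 150 per group reproduces with no credit for any covariate.

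**Conclusion.** The point holds as a low-priority efficiency recommendation. As stated, the primary and secondary models name neither the stratification factor nor laterality, so the intervals will be wider than necessary if either predicts outcome.

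For laterality, under the assumed ranges the gain runs from 0.1 to about 4 points of power, and is about 1 point mid-range. It disappears if the two groups do not differ in KOOS-ADL. For site, the documents give no figure from which to judge the gain. There is no error, contradiction or bias here. The reason to act is that the change costs almost nothing and is best prespecified before the final analysis.

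**What to change.** Before the final analysis, state in the statistical analysis plan that the primary and secondary mixed models include, beside the baseline score, fixed effects for:

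- site;
- laterality (unilateral or bilateral) as planned at randomisation, or as performed where enrolment follows surgery, and not reclassified if the other knee is operated on later.

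Use a fixed effect for site, because two sites are too few to estimate a random-effect variance. Keep the laterality interaction as a separate subgroup test, so that the main estimate remains a single overall group difference.

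Cost: some wording and two model terms, one degree of freedom each. No new data should be needed: site is known from the randomisation, and the subgroup test already requires laterality, although the article does not list it as a collected item. The sample size is unchanged.

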### Study setting

This trial will be conducted at a publicly funded and a privately funded tertiary care hospital in Delhi, India. In these hospitals, the usual approach for rehabilitation after knee arthroplasty is a home-based rehabilitation protocol with outpatient visits when required. Typically, discharge to home happens 48–72 hours after surgery and patients are given a printed pamphlet with details of the exercises to be performed postsurgery. Patients are free to seek external physiotherapy support. The study hospitals cater to a vast geographic area in the Northern region of India and a sociodemographically diverse population. A single operating unit at each of the hospitals will participate in this trial and they perform approximately 15–20 primary knee arthroplasties in a month.

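### Randomisation is stratified by site, but the covariates named for the primary and secondary models do not include site; if site is prognostic, some precision is given up

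*Protocol article*

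**What the plan says.** **Allocation.** Assignment of interventions: "Permuted varying block randomisation with 1:1 allocation ratio stratified by trial site was generated using Stata V.18". No other stratification factor is given.

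**Sites.** Study setting: "This trial will be conducted at a publicly funded and a privately funded tertiary care hospital in Delhi, India". One operating unit takes part at each. The Interventions section adds that rehabilitation after discharge is not standardised at these hospitals, and Table 1 says that practice varies within and between hospitals.

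**Adjustment.** It is stated three times, each time without site:
- Outcomes, primary comparison: "compare the end value of KOOS-ADL score at 3 and 6 months independently between the two groups adjusted for baseline score".
- Statistical methods, primary analysis: "KOOS-ADL score at 3 and 6 months adjusted for baseline score will be calculated using mixed effect linear regression".
- Statistical methods, secondary continuous outcomes: "linear mixed effect method adjusted for baseline KOOS-ADL, as performance-based measures will not be collected at baseline".

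The random effects of the mixed model are not described.

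**Error rate.** Sample size works "with an overall type I error rate (α) of 0.05", split over two time points. Statistical methods: "A p value of 0.025 will be considered as statistically significant for each of the time points".

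**Later plan.** Statistical methods: "A statistical analysis plan will be developed before the end of trial recruitment and made publicly available before final analysis". That plan is not at hand.

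**The concern.** An analysis should normally reflect the factor by which a trial randomises. Stratified 1:1 allocation balances the two hospitals across the arms, so a difference between hospitals contributes almost nothing to the true sampling variance of the treatment contrast. A model without site does not use this. It counts the hospital difference as residual noise and reports a standard error larger than the real one. Intervals are then wider than they need be, and the test rejects less often than its nominal level.

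This requires site to predict outcome after adjustment for baseline score. That is plausible with one public and one private hospital and locally varying rehabilitation, and baseline KOOS-ADL need not absorb such differences. It is an even weaker stand-in for site where the outcome is range of motion or a performance test. What is at stake is precision and the calibration of intervals, not the validity of a positive result.

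**Working it through.** **1. The plan's own figure.** From Sample size: d = 0.40, marginal power 85%, two-sided, Bonferroni over two time points (0.025 each), 10% loss to follow-up.

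n per arm = 2 × (z₀.₉₈₇₅ + z₀.₈₅)² / d² = 2 × (2.2414 + 1.0364)² / 0.16 = 134.3, so 135. After loss: 135 / 0.90 = 150. The stated figure of about 150 per arm reproduces.

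**2. Inputs for the site question.**
- Total SD 15 (Sample size gives it as the common SD of each group).
- n = 135 analysed per arm; α = 0.025 two-sided, z = 2.2414.
- Treatment effect 0.40 × 15 = 6 points, the effect that the sample size uses. The section also names 7 points, and 7/15 = 0.467. That mismatch is a separate matter.
- Site difference D in mean KOOS-ADL, and a 50:50 split between hospitals. Both are assumptions. The documents give no value for D, so a range is shown.

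**3. Formulas.** With equal sites, between-site variance is (D/2)².
- Within-site SD: s = √(225 − D²/4)
- SE reported without site: 15 × √(2/135) = 1.826
- True SE under stratification, which is also the SE with site in the model: s × √(2/135)
- Actual type I error without site: 2 × [1 − Φ(2.2414 × SE ratio)]
- Power without site: Φ[(6 − 2.2414 × 1.826) / true SE]
- Power with site: Φ[6 / true SE − 2.2414]

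**4. Example, D = 10.** s = √(225 − 25) = 14.14 and true SE = 1.721. The SE ratio is 1.826 / 1.721 = 1.061. Type I error = 2 × [1 − Φ(2.377)] = 0.017. Power without site = Φ(1.108) = 86.6%; with site = Φ(1.244) = 89.3%.

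**5. Range.**

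| Site difference D | SE ratio | Actual type I error | Power without site | Power with site |
|---|---|---|---|---|
| 0 | 1.000 | 0.025 | 85.2% | 85.2% |
| 3 | 1.005 | 0.024 | 85.3% | 85.6% |
| 5 | 1.014 | 0.023 | 85.5% | 86.2% |
| 7 | 1.028 | 0.021 | 85.9% | 87.2% |
| 10 | 1.061 | 0.017 | 86.6% | 89.3% |
| 15 | 1.155 | 0.010 | 88.6% | 94.0% |

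A 15-point difference is a full SD. Nothing in the documents supports one that large; the row only shows the limit.

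**6. Check with baseline adjustment.** A simulation compared ANCOVA with and without site (4,000 runs, 272 analysed, assumed baseline correlation 0.4, 6-point effect). At D = 5, power was 91.2% without site and 92.0% with it. At D = 10 it was 91.9% and 94.0%, with mean SE 1.67 and 1.56. The direction and rough size agree with the table.

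**The case against.** The strongest reply is that the article is silent on site and does not exclude it. It specifies a mixed model without describing the random effects, and it announces a public statistical analysis plan. Site may be a term in that model already, and full model specification is commonly left to such a plan. This stands in part: nobody can say from this text that site will be left out. But the article did not leave adjustment open. It names the covariate set three times, even gives a reason for the secondary one, and the stratification factor is not in it.

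Three stronger readings are tempting, and the documents do not support them.

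- **That the planned 85% power is lost.** A reader who takes 15 as the within-site SD and adds site variance on top gets a total SD of 15.2, 15.8 or 16.8 for site differences of 5, 10 or 15 points, and power of about 84%, 82% or 78%. But the sample size rests on a two-sample t-test with a common SD of 15 for each whole group and no site term. On that basis power without site stays at or above 85% in every row of the table.
- **That a random site effect would not help with only two sites.** The site variance would indeed be poorly estimated, but the treatment contrast is balanced within site and hardly depends on it. In a simulation of 270 patients at two sites (stratified 1:1 allocation, within-site SD 15, 10-point site difference, 200 runs), the mean treatment SE was 1.93 without site, 1.83 with fixed site and 1.83 with random site. If the undescribed mixed model contains a random site intercept, the loss disappears.
- **That standard errors are certainly too large.** This holds only if site predicts outcome after baseline adjustment. For differences of 0 to 5 points the overstatement is at most 1.4%.

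**Conclusion.** The point holds as one about precision. The trial stratifies by site, and the adjustment sets stated for the primary and secondary models do not name site. If the models are run as stated, and the hospitals differ after baseline adjustment, the standard error is overstated by about 1.4% at a 5-point difference and 6% at 10 points. The power given up relative to a site-adjusted model is about 1 and 3 percentage points.

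These sizes rest on an assumed site difference, equal enrolment at the two hospitals, a total SD of 15, 135 analysed per arm and a 6-point effect. The error is on the conservative side: the treatment estimate is not biased, and a positive result would not be called into question. The case for acting is that the improvement is almost free and is best made before outcome data are analysed.

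**What to change.** State in the statistical analysis plan, before the final analysis, that site enters the primary KOOS-ADL model as a fixed covariate, with a site-by-time term because two time points are modelled together. Do the same in the models for the secondary continuous outcomes. Include site in the imputation model, should the multiple imputation planned for losses above 5% be triggered. Describe the random effects at the same time, so that the role of site is unambiguous.

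A fixed effect is the simpler choice with two hospitals, since it needs no variance estimate from two levels. The cost is one degree of freedom for site and one for site-by-time, which is negligible with 300 participants. No change to sample size, data collection or conduct is needed. Prespecification matters in an open-label trial: a site term added after results are known could look like model selection.
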